#### Statistical analyses

Descriptive statistics will be calculated for all variables per site and as summary measures across sites. Continuous and count variables will be summarised by mean and SD, or median and IQR in case of skewed data. Binary and categorical variables will be summarised through counts and percentages. CIs and prediction intervals will be calculated for the two feasibility endpoints (recruitment efficacy and percentage of retention in the trial) in addition.

We acknowledge that this feasibility RCT is not powered to detect any statistically significant effects. Nevertheless, explorative analyses will be undertaken at the cluster-level and the individual-level to evaluate the effects of the intervention on the secondary outcome variables using two-sample hypothesis tests, random effects models and generalised estimation equations, as appropriate. Alongside point-estimates, p values and 95% CIs will be reported.

Missing data will be explored to understand why they are unavailable; when missing data are due to incomplete follow-up survival or censored regression analyses will be considered, otherwise multiple imputation with chained equations or Bayesian imputation will be applied. The intraclass correlation coefficient will be calculated for the secondary endpoints to inform subsequent sample size and power calculations.

All the analyses will be undertaken using statistical software packages Stan,^36^ R and Stata (StataCorp College Station, Texas, USA: StataCorp).

#### Qualitative data analysis of interviews addressed to medical assistants

All interviews will be de-identified, transcribed verbatim and analysed by at least two researchers inductively via content-analysis inspired by Kuckartz.^37^ The analysts perform first line-by-line coding after extensive reading of the interviews (familiarisation). While iteratively refining the code labels, they are grouped to generate categories and subcategories. In subsequent iterations of the process, categories and subcategories are refined in light of the research question and are summarised in a final report of the analyses.

#### Sample size considerations

An ad hoc analysis undertaken on claims data provided by the Bavarian health insurance union (Kassenärztliche Vereinigung) covering all diagnosed UTIs in ambulatory care from 2015 to 2019 showed that each GP had an average of 60 encounters for uUTI in women aged 18–70 per year, with only slight seasonal fluctuations (data not shown). Considering that some of these encounters occur in out-of-hours care and that not all of the patients presenting with uUTI are going to be eligible, we expect that 200 patients in both arms (ie, 100 patients per arm=an average of 10 enrolled patients in each of the 20 clusters) is a reasonably achievable sample within 6 months of trial duration.

Assuming that the percentage of complete follow-up is 75% in the population the patients are sampled from, a simulation study showed that the 200 patients of the feasibility trial enable the estimation of the percentage of complete follow-up with a 95% CI of width of less than 13% with a likelihood of 0.90.

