**Methods and analysis:**

This is an open-label two-arm parallel cluster-randomised controlled pilot trial. 20 general practices affiliated with the Bavarian Practice-Based Research Network (BayFoNet) in Germany were randomly assigned to deliver patient management based on POCTs or to provide usual care. POCTs consist of phase-contrast microscopy to detect bacteria and urinary dipsticks to detect erythrocytes in urine samples. In both arms, urine samples will be obtained at presentation for POCTs (intervention arm only) and microbiological analysis. Women will be followed-up for 28 days from enrolment using self-reported symptom diaries, telephone follow-up and a review of the electronic medical record. Primary outcomes are feasibility of patient enrolment and retention rates per site, which will be summarised by means and SDs, with corresponding confidence and prediction intervals. Secondary outcomes include antibiotic use for UTI at day 28, time to symptom resolution, symptom burden, number of recurrent and upper UTIs and re-consultations and diagnostic accuracy of POCTs versus urine culture as the reference standard. These outcomes will be explored at cluster-levels and individual-levels using descriptive statistics, two-sample hypothesis tests and mixed effects models or generalised estimation equations.

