### Objectives

#### Primary objective

The primary objective of this study is to assess the feasibility of a full-scaled diagnostic RCT. The primary endpoints are patient recruitment efficacy and the percentage of retention in the trial. Recruitment efficacy will be calculated as the number of participants enrolled per site over the 6 months of trial duration, and retention as the percentage of complete follow-ups per site over 28 days. A confirmatory study without major design changes will be considered feasible if study sites recruit 10 patients each and patients lost to follow-up do not exceed 20%.

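### The retention precision (95% CI under 13 points with likelihood 0.90) matches 200 independent women, not 20 practices summarised per site

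*Protocol article*

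**What the plan says.** All references are to the protocol article.

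- **Sample size considerations.** The target is "100 patients per arm=an average of 10 enrolled patients in each of the 20 clusters", 200 women in all. The precision statement starts "Assuming that the percentage of complete follow-up is 75% in the population the patients are sampled from" and says that a simulation showed 200 patients to "enable the estimation of the percentage of complete follow-up with a 95% CI of width of less than 13% with a likelihood of 0.90". No ICC, design effect or between-site variance for retention is given there or elsewhere.
- **Primary objective.** The endpoint is "retention as the percentage of complete follow-ups per site over 28 days". One of the two feasibility criteria is that "patients lost to follow-up do not exceed 20" percent.
- **Abstract, Methods and analysis.** The primary outcomes include "retention rates per site, which will be summarised by means and SDs, with corresponding confidence and prediction intervals".
- **Statistical analyses.** "CIs and prediction intervals will be calculated for the two feasibility endpoints", with no interval method named. On clustering: "The intraclass correlation coefficient will be calculated for the secondary endpoints to inform subsequent sample size and power calculations". Retention is a primary endpoint, so it falls outside that sentence.

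**The concern.** The width is stated for a number of patients, whereas the endpoint is defined, summarised and given a prediction interval across practices. An interval built from the mean and SD of 20 site percentages differs from a binomial interval on 200 women in two ways. It carries any real variation in retention between practices. Its standard error is also estimated from only 20 values, so the width itself varies from one realisation to the next, even if practices do not truly differ.

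What is at stake is the uncertainty shown around one of the two primary feasibility endpoints. The planning value of 75% lies 5 points below the 80% retention implied by the loss criterion, so a reader weighing the observed rate against 80% needs an honest interval. The reported interval will either be wider than announced or, if women are pooled as independent, will cover less than 95% when retention clusters by practice.

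**Working it through.** **Inputs.** From the article: true retention p = 0.75; n = 200; k = 20 sites; mean site size m = 10; confidence level 95%; width limit 0.13; stated likelihood 0.90. Assumed, because the article gives none: ICC for retention of 0, 0.01, 0.02, 0.05 and 0.10.

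**Step 1: reproduce the stated figure with independent women.** Take X ~ Binomial(200, 0.75) and add up the probability of every X whose 95% interval is narrower than 0.13.

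- Clopper-Pearson: the width is 0.124 at X = 150. It is below 0.13 for X = 143 and above in the relevant range. P(width < 0.13) = 0.889, and the 90th percentile of the width is 0.130. This matches the claim.
- Wald 0.993; Wilson 0.997; Jeffreys 0.996. The claim holds for these too, as a lower bound.

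**Step 2: expected width under clustering.** The design effect is 1 + (m − 1) × ICC = 1 + 9 × ICC, and the approximate width is 2 × q × √[p(1 − p)/n × design effect].

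At ICC 0 this is 2 × 1.96 × √(0.1875/200) = 0.120 with the normal quantile, and 2 × 2.093 × 0.0306 = 0.128 with t on 19 df. The second already lies close to the 0.13 limit.

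| ICC | Design effect | Effective n | Width, normal | Width, t(19) |
|---|---|---|---|---|
| 0.01 | 1.09 | 183 | 12.5 | 13.4 |
| 0.02 | 1.18 | 169 | 13.0 | 13.9 |
| 0.05 | 1.45 | 138 | 14.5 | 15.4 |
| 0.10 | 1.90 | 105 | 16.5 | 17.7 |

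**Step 3: likelihood of a width under 13 points when the SD comes from 20 sites.** Beta-binomial simulation, 100,000 runs, 20 sites of 10 women, interval = mean ± q × SD/√20.

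| ICC | P(<13), t(19) | P(<13), normal | Mean width, t(19) | 90th percentile, t(19) |
|---|---|---|---|---|
| 0 | 0.57 | 0.73 | 12.7 | 15.3 |
| 0.01 | 0.47 | 0.63 | 13.2 | 16.0 |
| 0.02 | 0.38 | 0.54 | 13.7 | 16.7 |
| 0.05 | 0.19 | 0.30 | 15.2 | 18.5 |
| 0.10 | 0.06 | 0.11 | 17.4 | 21.2 |

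A hand check agrees. The squared SD behaves roughly as a scaled chi-square on 19 df, so P(width < 0.13) ≈ P(χ²₁₉ < 19 × (0.13/expected width)²). At ICC 0 with t(19), 19 × (0.13/0.1282)² = 19.55 gives 0.58. At ICC 0.05, 19 × (0.13/0.1543)² = 13.48 gives 0.19.

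**Step 4: unequal sites.** With assumed sizes from 2 to 22 (total 200, coefficient of variation 0.53), a cluster-robust pooled t(19) interval is under 13 points with probability 0.60 at ICC 0, 0.39 at 0.02 and 0.20 at 0.05; its 90th-percentile widths are 15.5, 17.3 and 19.7 points. An unweighted mean of site percentages does worse: 0.22, 0.13 and 0.06.

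**Step 5: a pooled binomial interval instead.** It stays narrow: at ICC 0.05 the Wald width is under 13 points with probability 0.98. But coverage (Wilson, equal sites) is 94% at ICC 0.02, 91% at 0.05 and 86% at 0.10.

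**The case against.** Several points on the other side stand.

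- **The simulation is not shown.** Independence is inferred from the wording and from a close match with one interval method. A Wald or Wilson width inflated by a *known* design effect would still reach 0.90 up to an ICC of about 0.008 to 0.009: (0.13/0.1258)² = 1.068 and (0.13/0.1248)² = 1.085, and the excess over 1 divided by 9 gives 0.0076 and 0.0094. So it cannot be said that the figure holds only under strict independence.
- **The interval method is not fixed.** The t(19) interval is one reading of the mean-and-SD summary. The precision sentence itself speaks of a population of patients, which could point to a pooled percentage. With a normal quantile the shortfall is smaller, but the likelihood still stays below 0.90.
- **Retention may cluster weakly.** The reminder and day-28 calls are made by research nurses at two university departments, and university researchers review the records for missing follow-up. Diaries, however, are returned to the practices, so no clustering at all cannot be taken for granted. Nothing in the article supports an ICC as high as 0.10; it is only the upper end of the range shown.

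A reader might also infer more than the article supports. One might conclude that the sample size loses its basis; but 200 is justified by what is achievable from claims data within 6 months, and the precision sentence only describes what that number yields. One might conclude that the go/no-go decision is compromised; but the criterion is stated as a 20% loss threshold with no confidence bound. Nor is retention the only primary endpoint with a planning figure: recruitment has its average of 10 per practice.

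**Conclusion.** The precision sentence is wrong as written for this design. It is arithmetically right for 200 independent women, but a per-site interval from 20 practices does not deliver it at any ICC examined. At best (ICC 0, equal sites, normal quantile) the likelihood is about 0.73 rather than 0.90; at an assumed ICC of 0.05 it is 0.19 to 0.30. The direction does not depend on the ICC; the size does, and also on the interval method and the spread of site sizes, none of which the article fixes.

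The consequence is moderate. In a pilot with an achievability-based sample size and a feasibility criterion without a confidence bound, the damage is confined to how precisely retention is said to be estimated, and to a confirmatory cluster trial that would be planned from that estimate. It should be fixed; it does not invalidate the design.

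**What to change.** 1. Replace the precision sentence with a simulation that uses 20 sites, a stated ICC range and the interval that will be reported. For equal sites, t with 19 df and an assumed ICC of 0.02 to 0.10, it could read: expected 95% CI width about 14 to 17 points, with 17 to 21 points not exceeded with likelihood 0.90, and somewhat wider if site sizes are unequal.
2. State that the confidence interval for retention will allow for clustering by site, either from the site-level mean and SD or from a cluster-robust pooled estimate, and name which.
3. Add retention to the endpoints for which an ICC is reported, so that the confirmatory trial can use it.

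The cost is one repeated simulation, a reworded paragraph and a less favourable stated precision. The number of patients, the conduct of the trial and the feasibility criteria stay as they are, so the change can be made while recruitment is under way.

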#### Patient and public involvement

A citizens’ forum was established within the BayFoNet framework. Invited are all citizens who are interested in contributing to research projects of the Department of General Practice (University Hospital Würzburg). All important steps that are necessary for different projects and studies are discussed with the participants.

The MicUTI study has been discussed with the citizens twice so far. After the presentation of the study, the participants discussed whether therapy for uUTI without antibiotics would be conceivable. In addition, the members gave feedback on the comprehensibility and clarity of the patient diary and the patient information.

Furthermore, feedback was given in the following meeting of the citizens’ forum on how the citizens’ comments were incorporated into the further work.

#### Trial status

Patient recruitment started in June 2023 and is ongoing. Planned end of patient recruitment is in April 2024.

## Ethics and dissemination

The study will be conducted in accordance to the Declaration of Helsinki in its current version.^38^ The University of Würzburg institutional review board approved MicUTI on 16 December 2022 (protocol n. 109/22-sc). The recording, disclosure, storage and analysis of personal data within this clinical trial will take place by the legal provisions of the European Union General Data Protection Regulation (GDPR). To protect the confidentiality, all data will be collected and stored psudonymised. Pseudonymisation lists will be stored in a secure place at each study sites separately from CRFs.^39^ Details of procedures to ensure confidentiality are provided in the online supplemental file.

10.1136/bmjopen-2023-079345.supp1Supplementary data

A trial steering committee is established. The committee is composed by the principal investigator (IG), the study coordinator (PKK) and by internationally renowned experts in the implementation and conduction of pragmatic RCTs in primary care and research methodology (AH, AF, AH, GS, MHE). The committee provides an overall methodological supervision of the study and safeguards the interest of study participants. Any of its members will be informed of amendments to the protocol.

The implementation of MicUTI will generate the needed knowledge to plan a confirmatory, full-scaled trial, intended to reduce the clinical equipoise about rapid POCTs used to inform the clinical management of uUTIs in general practice. Study results will be disseminated through peer-reviewed publications, academic conferences, a report addresses to participating GPs and through a summary report in lay language addressed to patients and the public.
